#### Symptoms via doctor’s diagnosis

Primary care visits and physicians-diagnoses during the first year of life are recorded according to the International Classification system of Primary Care (ICPC) [40] and are traced through report of the computerized medical files recorded by the general practitioner.

Visits to the physician are defined as the occurrence of a “respiratory ICPC”, “gastrointestinal ICPC” or “dermatological ICPC”. For respiratory ICPC’s, these include dyspnea (R02), wheezing (R03), cough (R05), acute upper tract infection (R74), acute bronchi(oli)tis (R78), pneumonia (R81), asthma like symptoms (R96), or other less prevalent respiratory ICPC’s (breath problems [R04], sneeze [R07], other symptoms of the nose [R08], symptoms of the throat [R21], abnormal sputum [R25], concern about respiratory illness [R27], acute laryngitis [R77], influenza [R88], other infections of the airways [R83], and other respiratory diseases [R99]). For gastrointestinal ICPC’s these include infectious diarrhea (D70), vomiting (D10) and susceptible gastro-intestinal infection (D73). Dermatological ICPC’s include other symptoms/complaints of the skin (S21), dry skin/flaking (S21.01). A child is considered to have eczema when the doctors diagnose was established and (1^st^ or 2^nd^ class) corticosteroids have been prescribed. Prescription will be checked via pharmacist’s medication records. The incidence of colic is recorded as ICPC infantile colic (A14).

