**Fig. 1 Fig1:**
[figure not shown]
Overview of the sample time points and outcomes

Potential differences in proportions (abundance and diversity) of intestinal bacterial groups (phyla) and species in antibiotic treated infants versus healthy controls will be determined by use of 16S-23S rRNA gene analysis. Secondly, we investigate differences in clinical outcomes between infants treated with antibiotics and controls. We evaluate incidences of atopic dermatitis (eczema), food allergy, upper respiratory tract infections (URTI), lower respiratory tract infections (LRTI), gastrointestinal infections (GITI) and excessive crying, prospectively assessed by parental reports and retrospectively assessed by doctor’s diagnoses. The clinical endpoints will be linked to the developing intestinal microbiota during the first year of life. Body mass index and standard deviation (SD)-scores are calculated from individual weight and height curves.

Parents of all included infants will report the use of antibiotics (type of antibiotics and duration of treatment) during the complete study period (i.e. the first year of life) on the calendar lists. Moreover, (the type of) prescribed antibiotics will be investigated at the end of the initial study period by approaching the infant’s pharmacy on medications used in the first year of life. Parents are also asked to report the moment of stool collection (date) on the collection vial, so the investigators can calculate the time between antibiotic treatment and stool sample collection. We hypothesize that in early life antibiotic treated infants develop more eczema during their first year than non-antibiotic treated infants (healthy controls). We also expect an increase in incidence of (parental reported as well as doctor’s diagnosed) food allergy, respiratory tract infections (RTI’s) and gastrointestinal tract infections (GITI’s) in infants treated with antibiotics compared to controls.

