### Outcomes

#### Symptoms via calendar checklist

Parents are instructed to record a (for this study) designed daily checklist of clinical symptoms, which include coughing, wheezing, fever >38 °C, runny nose, glue ear, rash, diarrhea, >3 h of crying within one day (24 h). Table 1 shows the various symptoms, which should be recorded by the parents. Descriptions standardize the way of recording as much as possible. The checklists are designed as a calendar and parents are requested to return a list (at the end of) every month. As a motivation for returning the list, we send back a contemporary Dutch magazine for young parents, monthly, after receiving their list.

**Table 1 Tab1:** Description of symptoms

Coughing	Your infant coughs several times a day and/or has coughing. Regularly there are signs of cold. Don’t record cough because of choking.
Wheezing	During expiration you notice a whistling, wheezy sound coming from the lower airways. During expiration your child is trying to squeeze the air outwards. Don’t record wheezing coming from or through the nose.
Fever >38 °C	Clear from itself, whereby it is important you use a rectal thermometer, measure twice and the temperature is >38 °C on both occasions.
Runny nose	Signs of cold with white/yellow/green mucus running from the nose;
Glue ear	Your child seems to have earache and/or grasps its ear (the ear frequently is high-colored or bends) and/or glue egresses from the ear.
Rash	More than one day existing skin-redness (spots, rash, pimples) on the face, arms or legs, trunk. Disease-symptoms are not necessarily present. The rash can be eczema; eczema mostly is red, moistly, scaly and may itch. Infants cheeks are affected mostly. When children grow up, elbow and knees are preferred sites.
Diarrhea	Increase in stool frequency to twice the usual number per day, that continues more than one day. The content may be watery or mucous.
>3 crying hours a day	Clear from itself, whereby the total crying episodes add up to more than three hours a day (24 h) in total.

At baseline, parents have to fill out an online questionnaire containing questions on demographics, comorbidity and use of medication. This questionnaire includes: gestational age and birthweight of the child, maternal comorbidity (medication during pregnancy and delivery), environmental factors (habitat, housing), parental smoking habits, siblings, pets, chronic diseases and hereditary diseases, ethnicity, education.

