Regarding the daily checklists, RTI’s and GITI's are defined as follows: an episode of respiratory tract infection includes at least two consecutive days of coughing and/or wheezing, runny nose and/ or earache (with or without secretion). An episode ends when the child is symptom-free for at least two consecutive days. Diarrhea is defined as increase in stool frequency to twice the usual number per day, during at least two consecutive days. Parents also report visits to the general practitioner because of respiratory or gastrointestinal symptoms of their child (since particularly respiratory infection may have a confounding effect, as antibiotic use and respiratory infections are so common and closely related in early life) [39]. Parents are extensively instructed by one of the investigators, at baseline of the study, how to fill in the daily checklists and how to interpret their child’s symptoms.

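### Earache counts towards a parent-reported respiratory infection, but no ear code appears in the doctor-diagnosis lists, so a GP contact coded only as an ear problem is not counted there

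*Protocol article*

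**What the plan says.** Under Aims, the protocol article lists upper and lower respiratory tract infections among outcomes that are "prospectively assessed by parental reports and retrospectively assessed by doctor’s diagnoses". The same section states the hypothesis of a higher incidence of RTI in treated infants for both sources.

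*Parent version.* Under Symptoms via calendar checklist, an RTI episode requires "at least two consecutive days of coughing and/or wheezing, runny nose and/ or earache (with or without secretion"). Table 1 gives the ear its own daily item, glue ear, whose description begins "Your child seems to have earache and/or grasps its ear" and goes on to discharge from the ear.

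*Doctor version.* Under Symptoms via doctor's diagnosis, the section states: "Visits to the physician are defined as the occurrence of a “respiratory ICPC”, “gastrointestinal ICPC” or “dermatological ICPC". It then prints the codes for each category:
- The main respiratory codes are "dyspnea (R02), wheezing (R03), cough (R05), acute upper tract infection (R74), acute bronchi(oli)tis (R78), pneumonia (R81), asthma like symptoms (R96").
- The less prevalent respiratory codes begin with "breath problems [R04], sneeze [R07], other symptoms of the nose [R08], symptoms of the throat [R21], abnormal sputum [R25"], continue with R27, and end with "acute laryngitis [R77], influenza [R88], other infections of the airways [R83], and other respiratory diseases [R99"].
- The gastrointestinal codes are "infectious diarrhea (D70), vomiting (D10) and susceptible gastro-intestinal infection (D73").
- The dermatological codes are S21 and S21.01. Infantile colic is recorded separately as A14.

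**The concern.** RTI is presented as one outcome with two sources, yet the two printed definitions do not cover the same illnesses. The calendar places ear symptoms inside RTI; the code lists leave them out of every category. An infant taken to the GP with an ear illness, and coded for that alone, can be a case in one version and a non-case in the other because of the definitions and not because of what parents or GPs noticed.

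At stake is how the doctor-based RTI result is read. Some disagreement between the sources would come from content and could not be separated from differences in ascertainment. Any effect of early antibiotics on GP-diagnosed ear illness would be absent from the doctor-based RTI outcome.

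**Working it through.** The plan states no figure on this point, so the check sets the two definitions side by side.

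**1. Qualifying symptoms in the calendar rule** (Symptoms via calendar checklist). There are four: coughing, wheezing, runny nose and earache. They are joined by and/or, so on the natural reading earache lasting at least two consecutive days qualifies by itself.

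**2. Codes in the doctor-diagnosis section.**

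| Group | Codes | Number | Naming the ear |
|---|---|---|---|
| Respiratory, main | R02, R03, R05, R74, R78, R81, R96 | 7 | 0 |
| Respiratory, less prevalent | R04, R07, R08, R21, R25, R27, R77, R88, R83, R99 | 10 | 0 |
| Gastrointestinal | D70, D10, D73 | 3 | 0 |
| Dermatological | S21, S21.01 | 2 | 0 |
| Colic | A14 | 1 | 0 |

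Respiratory total: 7 + 10 = 17, with 0 naming the ear. All codes: 17 + 3 + 2 + 1 = 23, with 0 naming the ear.

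**3. Both rules applied to three illustrative records.**

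| Record | Calendar RTI | Doctor-based respiratory category |
|---|---|---|
| Three days of cough, GP codes R05 | yes | yes |
| Three days of ear discharge, GP codes an ear problem and also R74 | yes | yes |
| Three days of ear discharge, GP codes an ear problem only | yes | no |

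Only the third record is discordant by definition. As printed, it falls outside all three visit categories, not just the respiratory one.

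**4. Size.** Let *s* be the share of GP contacts that would meet an ear-inclusive RTI definition but carry only an ear code. The printed list then captures a fraction 1 − *s* of those contacts. The documents give no value for *s* and no ear-infection rate from which to derive one. If the outcome is analysed per child (any RTI in the year), a child with an ear-only contact is still a case when any other contact in that year carries a listed R-code.

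**The case against.** **The list defines visit categories, not infections.** It includes items that are not infections, such as dyspnea, sneeze and concern about respiratory illness, and the article nowhere maps codes to URTI or LRTI. This is correct. It means the doctor-diagnosed RTI outcome has no printed definition other than this list. It does not bring ear contacts in.

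**The list may be open, and an article condenses a fuller protocol.** The codes are introduced as what the category includes, which could be read as examples. But the section names the common codes, then the rarer ones individually, and finishes with a residual code (R99), so it reads as complete. Nor is this a detail left out: both definitions are printed, and they differ. A fuller document may contain ear codes; if so, the article should say so.

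**Ear illness is not lost from the study.** The glue ear item records it daily, the GP files are traced, and respiratory disease episodes are discussed at the one-year visit. This stands. The gap is confined to one derived measure.

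**Stronger readings that a reader might infer:**
- *Later antibiotic courses would appear without a recorded infection behind them.* Not supported. Courses come from the calendars, the pharmacy and the clinic visit, and the Statistical analysis section groups children by number of courses without using an indication.
- *One measure cannot corroborate the other.* This goes too far. A symptom diary and GP-coded contacts were never going to agree exactly, and both can still show a group difference in the same direction.
- *The antibiotic effect on doctor-diagnosed RTI is biased.* Not shown. The same codes apply to both groups, and the planned measures are odds or hazard ratios between them.

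**Conclusion.** The mismatch is real and limited. Ear symptoms are part of RTI in the calendar definition, and no ear code appears among the 17 respiratory codes or the 23 codes in total. GP contacts coded only as an ear problem therefore do not count in the doctor-based measure of an outcome hypothesised for both sources.

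This rests on two readings: that earache alone satisfies the calendar rule, and that the printed code list is complete. The size of the loss cannot be computed; a reader might want to attach a percentage to the understatement, but the documents offer nothing to anchor one.

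Severity is minor to moderate. RTI is one of several clinical outcomes, and the Power calculation section bases the sample size on eczema, so the planned 450 infants are not affected.

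**What to change.** Align the two definitions. Add the ear-symptom and ear-infection ICPC codes to the doctor-diagnosed RTI definition, and report RTI from both sources with and without ear events as a sensitivity analysis. Settle this before outcomes are compared between the groups.

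If the sponsor prefers to keep the respiratory category as printed, the alternative is to take ear symptoms out of the calendar RTI rule as well and analyse ear events separately in both sources. If a fuller protocol already includes ear codes, one sentence stating this is enough.

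The cost is an edit to the code list. The GP files are already being traced, so no new data source is needed. The downside is a slightly broader outcome. The match will also remain imperfect, because the parents' ear item is less specific than a GP diagnosis; the analysis without ear events shows how much depends on it.

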#### Outpatient clinic visits

Shortly after the child’s first birthday, all children visit the outpatient clinic of the recruiting hospital and parents are asked to bring the collected, frozen fecal samples (on ice). Disease episodes (as to the respiratory tract and gastrointestinal tract) during the first year of life are discussed and documented. Any prescribed (systemic) antibiotic treatments during the first year of life as well as well as use of probiotics are recorded. At the end of the visit, a venapuncture is performed to collect a 1 ml blood sample. Serum is stored at −20 °C. At the end of the study, IgG antibodies against Tetanus toxoid, Diphtheria toxoid, *Haemophilus influenza* type B, and the capsular polysaccharides of the pneumococcal 10-valent conjugate vaccine will be determined. From the same blood sample, specific IgE to food and inhalant allergens is determined for objective evaluation of allergic sensitization.

#### Collection of fecal samples

Parents collect a total of 8 fecal samples during the first year of life, and one sample at or around the 2^nd^ birthday of the child. Directly after birth, nurses of the maternity and neonatal wards collect the first fecal samples, which are frozen at −20 °C. After discharge the parents start collecting samples at home. Collection of stool samples is standardized (oral instruction by the investigators at time of inclusion and there is a written instruction on the daily checklist of symptoms, that parents receive).

Parents are instructed to sample directly from the diaper by means of stool collection vials (with integrated spoons), and immediately freeze them in their home freezers at a temperature of −18 to −20 °C. Moreover, in order to be able to study transmission of microbiota from the parents to the child, mother collects a stool sample of her own within the first week after the delivery and a buccal mucous membrane swab and a skin swab from the mother and the father are taken at inclusion.

#### 16S-23S IS profiling of the microbiota

The stool samples are subjected to microbiota composition profiling by means of a high-throughput bacterial profiling technique (IS-pro, IS-Diagnostics, Amsterdam, The Netherlands). This technique combines bacterial species differentiation by the length of 16S-23S rRNA interspace region with instant taxonomic classification by phylum-specific fluorescent labeling of PCR-primers. For amplification of IS regions, phylum-specific, fluorescently labeled primers are designed, corresponding to conserved regions within the 16S rRNA and 23S rRNA genes [41]. The procedure consists of two multiplex PCRs, a combination of which provides very broad coverage for *Firmicutes*, *Actinobacteria*, *Fusobacteria* and *Verrucomicrobia* (FAFV), *Bacteroidetes* and *Proteobacteria*. Amplifications are carried out on a GeneAmp PCR system 9700 (Applied Biosystems, Foster City, CA, USA).

Buccal mucous membrane and skin swabs are analyzed by using the same IS-pro technique.

### Data analysis

After pre-processing (IS-pro software suite, IS-Diagnostics), each sample is represented by a microbial profile, consisting of color-labelled peaks. Each peak is characterized by a specific IS fragment (measured as nucleotide length) and a color related to a specific phylum group. The intensity of peaks reflects the relative quantity of PCR product (measured in relative fluorescent units). We further consider each peak as an operational taxonomic unit (OTU) and its corresponding intensity as relative abundance. Intensity values are log2 transformed when appropriate in order to compact the range of variation in peak heights, to reduce the dominance of abundant peaks and include less abundant species of the microbiota in downstream analyses and more related to the in vivo situation. This transformation results in improved consistency of the estimated correlation coefficient, lower impact of inter-run variation, and improved detection of less prominent species. This conversion is used in all downstream analyses, such as calculating within-sample and between-sample microbial diversity [41].

### Statistical analysis

We will evaluate the potential relationships between antibiotic use in early life and the various (clinical) endpoints. Variables are verified for normal distribution and *t*-tests will be used for testing the null hypothesis. Either logistic regression analysis or cox regression analysis will be applied to the data (appearance of the primary endpoint(s) will be recorded as specifically as possible), so that odds ratios or hazard ratios and their 95 % confidence interval can be presented for description of the relationships. Multivariate models will be used to assess confounders and confounding effects. We will perform post hoc analyses to look for potential effects of the different antibiotic regimes. Outcomes may, possibly, be classified into subgroups. According to antibiotic treatment after the first two weeks, children will be grouped based on the number of antibiotic courses during the first year of life (0 / 1 / 2 or more courses). Within the ‘treatment groups’ a distinction can be made between the class or spectrum of the prescribed antibiotics.

Microbiota composition will be described by means of abundance, diversity and (dis)similarity. Diversity is calculated using the Shannon index [42] and differences in this index will be tested with Mann–Whitney *U* test. Dissimilarities between samples, or between-sample diversity, are calculated as the cosine distance between each pair of samples and analyzed with principal coordinate analysis (PCoA). All statistical analysis will be conducted using SPSS version 22.0 (SPSS Inc., Chicago, IL, USA) and the vegan software package in R (Foundation for Statistical Computing, Vienna, Austria).

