### Aims

Healthy newborns born in the hospital, observed for low probability of neonatal infection will be compared to newborns exposed to antibiotic therapy in early life (first 1–2 weeks) by investigating potential differences in fecal microbiota composition. For this purpose fecal bacterial composition and diversity is determined at eight time points during the first year of life, from birth on: day one (T1), day two (T2), one week (T3), two weeks (T4), one month (T5), three months (T6), six months (T7), one year (T8). An overview of the sample time points and outcomes is shown in Fig. 1.

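### Grouping infants by antibiotic courses over the same year in which infections are counted (0 / 1 / 2 or more) builds a spurious gradient into the infection outcomes

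*Protocol article*

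**What the plan says.** The Statistical analysis section first sets out the relation between early-life antibiotic use and the clinical endpoints, with logistic or Cox regression and multivariable models for confounding. It then adds a second classification, based on treatment given after the first two weeks: "children will be grouped based on the number of antibiotic courses during the first year of life", in three levels (0, 1, 2 or more). It does not say which outcomes will be compared across these levels. It gives no lag, landmark or time-varying term.

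The outcomes run over the same period. Under Aims, "The clinical endpoints will be linked to the developing intestinal microbiota during the first year of life". The calendar-checklist section defines the infection outcome so that "an episode of respiratory tract infection includes at least two consecutive days of coughing and/or wheezing, runny nose and/ or earache", recorded daily through the year. That section also explains why general-practitioner visits are recorded: "since particularly respiratory infection may have a confounding effect, as antibiotic use and respiratory infections are so common and closely related in early life".

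Antibiotic use is reported by parents on the calendar lists, and "prescribed antibiotics will be investigated at the end of the initial study period" through the infant's pharmacy. Stool dates are recorded so that the interval from antibiotic treatment to sample can be calculated.

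**The concern.** A course given for a respiratory infection is a consequence of that infection. If infants are sorted by courses in weeks 3 to 52 and their RTI episodes over the same year are then compared, part of what is compared is the outcome with itself. More episodes give more chances of a course, so the group with 2 or more courses must contain the infants with more episodes, whatever antibiotics do.

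The error runs in the direction of the hypothesis. The Aims section expects more RTIs and GITIs in antibiotic-treated infants, so a rising pattern over 0, 1 and 2 or more courses would be read as support. General covariate adjustment does not repair an exposure that the outcome has partly produced.

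**Working it through.** The document gives no figure for this grouping, so there is none to reproduce. It also gives no episode rate and no fraction of episodes treated. Both are assumed below and varied.

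**1. Equal susceptibility, closed form.** Let N be RTI episodes in the year, Poisson with mean 5. Each leads to a course with probability p, and antibiotics have no effect on anything. Then courses C are Poisson with mean m = 5p, and untreated episodes N − C are independent Poisson with mean 5(1 − p). Hence E[N | C = c] = 5(1 − p) + c, and E[C | C ≥ 2] = m(1 − e^−m) / (1 − e^−m − m·e^−m).

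- p = 0.10, m = 0.5: E[C | C ≥ 2] = 0.1967 / 0.0902 = 2.18. Mean episodes are 4.50 (0 courses), 5.50 (1) and 4.50 + 2.18 = 6.68 (2 or more). Ratio of 2 or more to 0: 6.68 / 4.50 = 1.48.
- p = 0.20, m = 1: E[C | C ≥ 2] = 0.6321 / 0.2642 = 2.39. Mean episodes are 4.00, 5.00 and 6.39. Ratio: 1.60.

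**2. Unequal susceptibility.** Let the infant's rate be gamma with mean 5 and dispersion 0.4 (shape k = 2.5). Then E[N | C = c] = c + (1 − p)(k + c)/(k/5 + p), and C is negative binomial.

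- p = 0.10: P(0) = 0.634, P(1) = 0.264, so mean C in the top group is (0.5 − 0.264)/0.102 = 2.31. Episodes with 0 courses: 0.9 × 2.5/0.6 = 3.75. With 2 or more: 2.31 + 0.9 × 4.81/0.6 = 9.53. Ratio: 2.54.
- p = 0.20: P(0) = 0.431, P(1) = 0.308, mean C in the top group 0.692/0.261 = 2.65. Episodes: 0.8 × 2.5/0.7 = 2.86 against 2.65 + 0.8 × 5.15/0.7 = 8.54. Ratio: 2.99.

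**3. How often a test would be falsely positive.** This is a simulation with 382 evaluable infants (450 × 0.85, from the Power calculation section), mean 2 to 6 episodes, equal risk or gamma shape 2, a few courses unrelated to infection, and a Kruskal–Wallis test at 5% with no antibiotic effect.

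| Share of RTI episodes treated | Rejection rate |
|---|---|
| 0 | 4–7% |
| 5% | 77–100% |
| 10–20% | 99% or more |

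The lowest value in the 5% row comes from a mean of 2 episodes and equal risk, where the top group is very small. A repeat run gave 72% there.

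**4. Eczema.** With 20% incidence (the Power calculation's control rate) and eczema unrelated to prescribing, rejection is 4–7%. If eczema triggers a course with probability 5, 10, 20 or 30%, rejection is 8, 14, 39 or 73%.

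**5. Does time order alone cure it?** Counting courses in the first half-year and RTI episodes in the second (a split chosen for illustration) gives 4–6% rejection when all infants share the same risk. With gamma shape 2 it still gives 16–100%, because infection-prone infants have more courses early and more infections late. Under this model, once the number of earlier episodes is held fixed, earlier courses carry no further information about susceptibility. Adjustment for prior infections therefore addresses what the lag leaves, provided prescribing does not also depend on severity.

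**The case against.** The strongest reply is that the grouping is peripheral. The stated hypothesis compares infants treated early in life with untreated infants. The grouping follows sentences on post hoc analyses and possible subgroups, names no outcome, and is not called a dose-response. Lag rules are also the kind of detail a condensed article leaves out. The protocol sees the link between infections and antibiotics, records visits because of it, and plans multivariable models.

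Much of this stands, and it limits the point. It does not remove it: the grouping is a stated rule, its window is the outcome window, and nothing excludes RTI or GITI.

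A reader might infer more than the documents support:

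- **That the main comparison is biased by this.** It is not. Early exposure is defined in the first days or weeks, and nothing in the Statistical analysis section puts later courses into that model.
- **That every outcome causes the exposure.** The article states the link for respiratory infection only. GITI is affected to the extent that such episodes lead to courses. Doctor-diagnosed eczema requires a corticosteroid prescription, not an antibiotic, and nothing shows that food allergy or stool composition prompts prescribing.
- **That there is immortal-time bias because infants must stay event-free to collect courses.** RTIs are recurrent and do not end follow-up, and here it is infants with events who collect courses. That requirement would push the other way.
- **That early stools will be labelled by later drugs.** The first four of the eight samples fall at or before two weeks, before the counted courses, so such a comparison would be meaningless. But the article plans to calculate the antibiotic-to-stool interval. What is lacking is a sentence tying the grouping to it.

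**Conclusion.** The point holds for infection outcomes that prompt antibiotics, and for this secondary grouping only. Followed as written, the 0 / 1 / 2 or more comparison would show about 1.5–1.6 times as many RTI episodes in the top group with no antibiotic effect, given a mean of 5 episodes and 10–20% treated. With the assumed spread in susceptibility it would show 2.5–3.0 times as many. The sizes rest on assumed rates. The direction does not: a false gradient appeared throughout the range tried (mean 2–6 episodes, 5–20% treated).

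The early-life comparison and the sample size are untouched, and eczema is at risk only through any courses it triggers. Severity is moderate.

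**What to change.** Amend the sentence on grouping before analysis:

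- **Clinical outcomes:** enter courses after the first two weeks as a time-varying exposure with a pre-specified lag, counting only courses started before the onset of the outcome episode, and adjust for the number of prior infection episodes. The lag alone is not enough (step 5 of the working).
- **Stool samples:** count only courses before the sample date, using the interval the Aims section already provides for.
- **Otherwise:** keep the 0 / 1 / 2 or more table as description only, and state that no effect will be inferred from it for RTI or GITI.

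The daily calendars, parental antibiotic reports, pharmacy records and stool dates are already being collected, so no new data are needed. The cost is extra programming and somewhat wider intervals for this secondary question, since fewer courses count as exposure. Some confounding can remain if prescribing follows severity, and the report should say so.
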